## **1. Summary**

### **1.1. Aims**

The aim of this study is to assess the effect of alginate on iron absorption. This will be achieved by measuring the absorption of iron, in the form of ferrous gluconate encapsulated in alginate beads compared with non-encapsulated iron i.e. without alginate. In addition, the modulating effect of calcium (a known inhibitor of iron absorption) will be measured since calcium also forms strong complexes with alginate. The development and production of the iron beads is novel research currently being undertaken by colleagues at the Institute of Food Research. Therefore, this study will employ standard analytical techniques to evaluate iron absorption in the context of a novel iron delivery system.

### **1.2. Approach**

When combined with ascorbic acid, ferrous gluconate is an iron compound that has been reported to be an effective food fortificant, which may reduce the prevalence of anaemia. In order to maximise iron absorption *in vivo*, it would be advantageous to employ a delivery system that will protect the iron from adverse interactions in the gut lumen and deliver iron directly to the duodenum. This study aims to investigate the effectiveness of using an environmentally-responsive impermeable alginate barrier to deliver ferrous gluconate to the duodenum, thus maximising its availability for absorption.

#### **1.2.1. Study design**

The study design and outline are presented in Figures 1 and 2. This study is designed as a randomised, single blinded, cross-over trial with participants randomly allocated into two groups: A (n= 8 volunteers) and B (n=8 volunteers). For statistical power of this study please refer to section 14.1. By administration of test meals 1 and 4 scientist will investigate the possible protective effect of alginate on iron absorption (primary outcome). By administration of test meal 2 and 3 the research team will investigate whether alginates can bind calcium (a well-known iron inhibitor) *in vivo*, thus diminish the potential negative effect of calcium on iron absorption (secondary aim).

Only half (8) of the volunteers will undergo treatments including calcium. Therefore group A will undergo all 4 tests, whereas group B will undergo 2 out of 4 tests.

This study will be undertaken to compare the absorption of iron (approximately 20mg) added to cola jelly (200ml) as ferrous gluconate incorporated into alginate beads (approx. 22.2g) (test meal 1), with iron at the same dose given as ferrous gluconate in a commercially available capsule along with a diet cola drink (200ml), (test meal 4). The third test for group A only (test meal 3) will involve consuming iron incorporated into the alginate beads (approx 22.2g) added to cola jelly (200ml), followed by 2 capsules, each filled with 300mg commercially available calcium phosphate powder (Freedav  
vitamins, USA,

<http://www.freedavitamins.com/index.php?p=product&id=120&parent=10> )

(600mg in total) in the form of calcium phosphate. Cook *et al* has shown that this dose and form of calcium was the most effective in iron inhibition. The addition of calcium will determine whether the alginate barrier can reduce or prevent the inhibitory effect of calcium on iron absorption. The fourth test (test meal 3) will involve consuming cola jelly (200ml), a ferrous gluconate capsule (approx. 20mg) and two calcium phosphate capsules (300mg of calcium in each capsule) followed by a diet cola drink (200ml).

The development of the iron-containing beads is novel on-going research and consequently the preparation of the iron-containing alginate beads imposes certain limitations on the proposed study design. Currently, iron incorporation into the alginate beads is within 15% of that predicted. Analysis of the iron (atomic absorption spectroscopy) incorporated into the alginate beads is a three day procedure, and long term storage method for the beads has not yet been established. These limitations mean that the sequence of the test meals cannot be randomised (Fig.1). Iron containing alginate beads will be prepared for each volunteer approx. 48 hours before the test meal and stored in a refrigerator in a food grade kitchen at 4°C. Sub-samples of each batch of beads administered to each volunteer will be collected and their iron content analysed using atomic absorption spectroscopy. Once the exact content of iron present in the beads administered to each specific volunteer in Test meal 1 and 2 is known (and recorded), exactly the same amount of ferrous

gluconate will be weighed into a capsule and administered to that volunteer in a subsequent test meal (Test meal 4 and 3 respectively) after a minimum 7 day wash-out period.

For each test meal an oral dose of iron (approximately 20mg), sufficient to perturb the normal serum iron concentration, will be given to apparently healthy adult volunteers after a 10 hour (overnight) fast.

All test meals will be prepared by a trained (holding a level 2 award in food safety in catering) member of the scientific staff in the Clinical Research Trial Unit kitchen. The four test meals will be as follows:

- Test meal 1 for all volunteers (group A and B): 200ml cola jelly prepared from 200ml cola (Coca-Cola), 10ml of commercially available Diet Cola flavoured Drink Concentrate (Sodastream, Lakeland) and gelatine ([name]) gelatine (from animal source, [name], UK) with the addition of ferrous gluconate (approx 20mg +/- 2mg) in alginate beads (approx. 22.2g) followed by 200ml of diet cola drink (Coca Cola) with 3 placebo capsules (filled with 50mg commercially available dextrose powder, 'Glucose Dextrose Powder', PharmacyNearU.com) acting as placebos for calcium and an iron capsules.)
- Test meal 2 for 8 volunteers only (group A): 200ml cola jelly prepared from 200ml cola (Coca-Cola), 10ml of commercially available Diet Cola flavoured Drink Concentrate (Sodastream, Lakeland) and gelatine (from animal source, [name]) with the addition of ferrous gluconate in alginate beads followed by 200ml of a diet cola drink (Coca Cola) with 2 commercially available capsules containing calcium phosphate, (Freeda vitamins, USA) (300mg of calcium in each capsule, in total 600mg of calcium) and one placebo capsule in place of the iron capsule.
- Test meal 3 for 8 volunteers only (group A) : 200ml cola jelly prepared as above without iron containing alginate beads(approx. 22.2g), 2 calcium capsules (as above) and 1 ferrous gluconate capsule (prepared exclusively for each volunteer to match the iron content in the alginate beads administered in test meal 2) followed by 200ml diet cola drink.

- Test meal 4 for all volunteers (group A and B): 200ml cola jelly prepared as above, 1 ferrous gluconate capsule (prepared exclusively for each volunteer to match the iron content in the alginate beads administered in test meal 1) followed by two dextrose (50mg of dextrose in each capsule) placebo capsules in place of the calcium capsules and 200ml of diet cola drink.

[figure not shown]

Figure 1. Study design

All appointments which volunteers will attend to (starting from initial interview through the screening and test visits) will take place in Clinical Research and Trials Unit (CRTU) based in the Norwich Medical School at the University of East Anglia. The CRTU provides all the required facilities and resources for performing human trials.

A trained nurse based in the CRTU will undertake the following clinical procedures. On each test meal day an intravenous (i.v.) cannula will be inserted into an appropriate peripheral vein in one of the volunteer's arms. The cannula will remain in situ for six hours. A baseline blood sample will be taken prior to consuming the test meals. Further blood samples (5ml each time) will then be taken 20, 40, 60, 80, 100, 120, 150, 180, 240, 300 and 360 min after ingestion of the test meals (described above) and collected into appropriate tubes for the preparation of serum. Serum iron concentrations will be measured in each sample using a colorimetric assay. Figure 2 provides a flow chart of the study outline.

Absorption will be calculated from the area under the iron serum appearance curve using a compartmental modelling approach

[figure not shown]

Figure 2. Flow chart of study outline.

### **1.2.2. Study Population**

Volunteers will be recruited from a target population of women of child-bearing age (18-45y) and men who are regular blood donors (18-65y) as these individuals generally have iron stores at the lower end of the normal range. Iron absorption is more efficient when ferritin stores are below  $<60\mu\text{g/L}$  and therefore this will maximize the sensitivity of the absorption test.

Female volunteers who decide to take part in the study will be asked by a study scientist at the start of each experimental day if they are menstruating and if they are not, then they will be asked how many days ago menstruation has completed. This information may help to explain potential fluctuations in ferritin levels and potential differences in iron appearance in the serum during different experimental days. Menstrual iron losses may affect biomarkers of iron status such as ferritin which may in turn affect iron absorption.

## **2. Scientific Background**

According to the World Health Organisation (WHO) more than 2 billion people worldwide suffer from anaemia. Iron deficiency anaemia accounts for 50% of all anaemias with infants, children and pre-menopausal women at most risk.

Both in developing and developed countries the consequences of anaemia result in significant health problems and economic cost.

Nutritional iron deficiency is the consequence of dietary iron being insufficient to meet physiological needs. Depending on the presence of dietary enhancers and inhibitors, non-haem (inorganic) iron absorption from the diet ranges between 1% and 15%. Therefore the cause of nutritional deficiency is often related to low bioavailability rather than inadequate intake of iron.

There is a well-justified use of iron fortification as a strategy to prevent iron deficiency anaemia. Food fortification with iron is recognised as a sustainable and realistic way to reduce the occurrence of iron deficiency. Nonetheless it is challenging to the food industry, mainly due to organoleptic changes during storage or preparation. Water soluble forms of iron are considered to be

more bioavailable than non-soluble iron compounds. However, the former often cause sensory problems when added to foods, while the latter cause fewer problems but are not generally well absorbed and are therefore ineffective as fortificants. A potential strategy for overcoming this problem is the use of water soluble iron compounds protected by a water resistant barrier which will prevent potential organoleptic changes of fortified foods. Preliminary, *in vitro* work using Caco-2 cells has been undertaken to establish the most promising protective barrier. Caco-2 cells are human gastrointestinal tumour cells originally isolated from a colon adenocarcinoma in 1974. The Caco-2 cell line has been shown to have long viability under culture conditions (thus reproducibility of experiments) and to share many characteristics of normal small intestine absorptive cells. Due to these properties Caco-2 cells have been used in various nutritional studies as a model for the human small intestine. The main advantage of using Caco-2 cells to investigate transport of micronutrients and their bioavailability is that they are derived from a human source unlike other techniques using rodent models. The Caco-2 cell model can be used along with a simulated digestion phase. Before application of the food matrix onto the dialysis membrane which is placed above Caco-2 cell monolayer, samples undergo simulated digestion phase which imitates the enzymatic phase of human digestion in the stomach and duodenum and associated changes in the pH.

Caco-2 cells combined with simulated digestion is a useful model system that attempts to imitate small intestinal conditions and is a valuable tool for screening different iron sources in order to rank them for potential bioavailability and for investigating mechanisms of nutrient absorption in humans.

In studies undertaken by the research team, addition of 1% (w/v) alginate solution was shown to have an enhancing effect on iron uptake in the *in vitro* Caco-2 cell model as measured by ferritin formation, a surrogate index of iron availability. Across 2 experiments with the use of 4 different alginates ferritin formation was on average 2.27 ( $\pm$ SD=0.42) fold greater in cells treated with 1% alginate solution (w/v) in the presence of iron when compared with cells treated with iron only. (For more details see Annex 1, chart A and B). Moreover, the data demonstrated that alginate beads containing ferrous

gluconate provided protection to the iron throughout the *in vitro* digestion process and delivered iron in an available form for uptake by Caco-2 cells. The protective/enhancing effect of alginate was equivalent to the enhancing effect of ascorbic acid at 1:2 (Fe:AA) ratio (For more details see Annex 1, chart C).

This possible enhancing effect of iron containing alginates occurring *in vitro* may be related to the preference of alginate to bind the calcium that is present in the cells treatment medium, thus avoiding the inhibitory effect of calcium. This hypothesis will be tested *in vivo* by the simultaneous administration of alginate beads containing ferrous gluconate and commercially available capsule with calcium phosphate powder.

Physico-chemical studies performed at the Institute of Food Research (IFR), Norwich have resulted in the selection of an appropriate alginate polymer to be tested *in vivo* in this study.

Alginates are natural biopolymers extracted from brown seaweed consisting of linear copolymers of (1→4) linked β-D-mannuronic acid (M) and its C-5 epimer α-L-glucuronic acid (G). With the added variable of polymer length, this class of polysaccharides exhibits a broad spectrum of physicochemical properties. This variation ultimately underlies why alginates are commonplace in multiple industrial processes and are of valuable use both in medicines and the food industry. Within the food industry alginates are widely used as gelling, thickening, emulsifying and stabilising agents and thus extensively found in products such as ice creams, jams, sauces and desserts. In addition alginates are also found in medicines, most notably anti-reflux medicines such as Gaviscon Advance™.

Alginates have been shown to bind divalent and trivalent cations and therefore may be a useful vehicle for soluble iron compounds used to fortify foods. In addition, it has also been demonstrated that alginates can form a stable complex with ferric iron over a range of different pH values. On the other hand, studies carried out in ileostomy subjects have shown that alginates can decrease iron absorption. However, this finding was not statistically significant probably due to a small sample size and/or the administration of alginate as a powder. In the present study alginate will be

dissolved in water at 0.5% (w/v) concentration and saturated in a calcium and iron bath during the formation of the beads.

### **3. Objectives**

The aim of this project is to measure the effect of alginate on the absorption of iron from ferrous gluconate and any modulating effect of calcium.

#### **Primary outcome:**

- The determination of iron absorption (by measuring serum iron appearance) from iron gluconate incorporated into alginate beads compared with that from unprotected ferrous gluconate.

#### **Secondary outcome:**

- A comparison of iron absorption from ferrous gluconate incorporated into alginate beads given with calcium (iron inhibitor) and from unprotected ferrous gluconate given with calcium.

### **4. Hypothesis**

The primary hypothesis is that the alginate in iron containing alginate beads will act as a protective barrier throughout the gastric phase of digestion, and thus will deliver more available iron for absorption into the mucosal cells of the duodenum than ferrous gluconate administered in a capsule.

In addition, the secondary hypothesis is that the alginate will bind calcium thus decrease its inhibitory effect on iron absorption.

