### **14.1. Statistical power**

Each volunteer will act as his/her own control, which will minimise the number of subjects required. The assumptions made for the power calculation to estimate the number of volunteers are that a difference of 2.5% in iron absorption between the 2 tests (primary outcome, test meal 1 and test meal 4) will be nutritionally significant. A minimum of 12 volunteers would be required to complete the study to detect a difference of 2.5% at a significance level of 0.05 for 80% power.

For the secondary aim, a minimum of 8 volunteers would be required to detect a significant difference in iron absorption of 3.3% between a test meal containing 20mg of iron as iron gluconate with calcium and a test meal containing 20mg of iron as iron gluconate with calcium and alginate beads (test meals 2 and 3). This assumes a power of 80%, a level of significance of 0.05 and standard deviation of differences (within pairs) of 2.8%

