### **14.2. Statistical method**

The primary outcome measure is the difference in iron (ferrous gluconate) absorption when consumed in a form of iron incorporated into alginate beads compared with the same amount of iron in an unprotected form i.e. not in alginate beads. The secondary outcome measure is the difference in iron

(ferrous gluconate) absorption when consumed in presence of calcium in a form of iron incorporated into alginate beads compared with the same amount of iron not in alginate beads in presence of calcium.

Paired, two-tailed Student's t test will be used to assess any significant differences in absorption (for the primary and secondary outcome measure). This method was found to be appropriate when assessing iron absorption in previous studies conducted at the Institute of Food Research.

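### The secondary hypothesis is that alginate weakens calcium's inhibition of iron absorption, but its test (meal 2 versus meal 3, both with calcium) cannot separate that from a general alginate effect

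*Protocol*

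**What the plan says.** Meal numbers follow the bulleted list in Section 1.2.1: meal 1 is beads, meal 2 beads plus calcium, meal 3 capsule plus calcium, meal 4 capsule. Group A (n = 8) takes all four; group B takes meals 1 and 4.

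- **The claim.** Section 4: "the secondary hypothesis is that the alginate will bind calcium thus decrease its inhibitory effect on iron absorption". Section 1.2.1 says the same of the design: "The addition of calcium will determine whether the alginate barrier can reduce or prevent the inhibitory effect of calcium on iron absorption".
- **The comparison.** The secondary outcome in Section 3 sets absorption from beads "given with calcium (iron inhibitor) and from unprotected ferrous gluconate given with calcium". Section 1.2.1 assigns the question to these two meals alone: "By administration of test meal 2 and 3 the research team will investigate whether alginates can bind calcium".
- **The test.** Section 14.2: "Paired, two-tailed Student's t test will be used to assess any significant differences in absorption", for both the primary and the secondary outcome.
- **The sample size.** Section 14.1: "a minimum of 8 volunteers would be required to detect a significant difference in iron absorption of 3.3" percentage points between meals 2 and 3, with an SD of within-pair differences of 2.8, two-sided 5% significance and 80% power.
- **The primary hypothesis.** Section 4 also predicts that beads "will deliver more available iron for absorption into the mucosal cells of the duodenum than ferrous gluconate administered in a capsule", by protection in the stomach and without any calcium capsule.

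No section plans to compare the bead-versus-capsule difference with calcium against the same difference without it.

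**The concern.** To say that alginate decreases calcium's inhibition is to say that calcium lowers absorption less from beads than from a capsule. Meals 2 and 3 both carry the 600 mg of calcium, so comparing them measures calcium's effect in neither form.

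The risk runs both ways. If the primary hypothesis is true, meal 2 will tend to exceed meal 3 even when alginate does nothing about calcium, and the plan would read that as support for the secondary hypothesis. If beads lower absorption overall, real protection from calcium could be cancelled out. Section 2 gives some reason to consider the second case: it cites an ileostomy study in which alginate reduced iron absorption, although not significantly.

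**Working it through.** **1. What the planned difference contains.** On an additive scale, let *a* be absorption from meal 4, *g* the general effect of beads, *c* calcium's inhibition with the capsule, and *D* the amount by which alginate reduces that inhibition.

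- Meal 4 = a; meal 1 = a + g; meal 3 = a − c; meal 2 = a + g − c + D.
- Meal 2 − meal 3 = g + D.
- Meal 1 − meal 4 = g.
- (meal 2 − meal 3) − (meal 1 − meal 4) = D.

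The hypothesis concerns D; the test addresses g + D.

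**2. The plan's own figure.** Inputs from Section 14.1: difference 3.3, SD 2.8, n = 8, two-sided 0.05. The noncentrality is 3.3/2.8 × √8 = 3.33 and the critical t on 7 df is 2.365. Power is 81.5%, and 8 is the smallest n that reaches 80%. The stated sample size is right for the comparison it names.

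**3. How often that test is significant when D = 0.** Same n and SD, with true mean difference g:

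| General effect g (points) | P(meal 2 vs meal 3 significant) |
|---|---|
| 1 | 14% |
| 2 | 41% |
| 2.5 (primary target, Section 14.1) | 58% |
| 3.3 | 81% |

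In the other direction, g = −3.3 with D = +3.3 gives a true meal 2 − meal 3 difference of zero.

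**4. Dependence on scale.** If calcium inhibits proportionally, g shrinks when calcium is present. Assuming 50% inhibition (not a figure in the protocol), 2.5 points become 1.25; the noncentrality is 1.25/2.8 × √8 = 1.26 and the rejection rate is about 19%. In that same case the additive D is 1.25 − 2.5 = −1.25, although there is no modification in ratio terms.

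**5. Precision of D in group A.** The protocol does not give the correlation ρ between the two pair differences. Assuming SD 2.8 for each, SD(D) = 2.8 × √(2(1 − ρ)).

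| ρ (assumed) | SD(D) | Power at 3.3, n = 8 | Detectable at 80% power: n = 8 | n = 7 | n = 6 |
|---|---|---|---|---|---|
| −0.25 | 4.43 | 44% | 5.12 | 5.63 | 6.35 |
| 0 | 3.96 | 53% | 4.58 | 5.04 | 5.68 |
| 0.25 | 3.43 | 65% | 3.96 | 4.36 | 4.92 |
| 0.5 | 2.80 | 81% | 3.24 | 3.56 | 4.02 |
| 0.75 | 1.98 | 98% | 2.29 | 2.52 | 2.84 |

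Section 5 expects 13 complete data sets from 16 volunteers. Pro rata, that is 8 × 13/16 = 6.5 in group A, so the columns for 6 and 7 are the realistic ones.

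**6. Order.** Group A takes meals 1, 2, 3, 4 at visits 3 to 6 in fixed order. A linear trend of b per visit adds (2 − 3)b = −b to meal 2 − meal 3, and (2 − 3)b − (1 − 4)b = +2b to D.

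**The case against.** The strongest reply is that the secondary outcome, its sample size and its test agree with one another. As a comparison of beads with capsule in the presence of calcium, the plan is coherent and n = 8 reproduces. The mismatch lies in the mechanism claimed in Sections 4 and 1.2.1, and rewording could cure it. This stands, and it is why the point is not graded higher.

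A reader might infer that the secondary test has a false-positive rate of 58%. It does not. The test keeps its 5% level for its own null, equal absorption from meals 2 and 3. The 58% is the chance of rejecting that null when it is false for a reason unrelated to calcium, and it rests on the additive scale.

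A reader might also infer that group A's four meals form a clean 2×2 and that D should replace meal 2 versus meal 3. The documents do not support that either:

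- D has about 53% power at 3.3 points if the pair differences are uncorrelated, and less after losses.
- D is more exposed than meal 2 − meal 3 to a trend over the fixed visit order (+2b against −b).
- Section 1.2.1 matches the iron dose only within the pairs 1/4 and 2/3. Bead loading is within 15% of prediction, and Section 9.1 expects 18 to 22 mg. Meal 2 − meal 1 and meal 3 − meal 4 therefore compare separately prepared doses.
- The beads are loaded in a calcium chloride bath (Section 9.2), so meal 1 is not free of calcium. Section 2 also suggests that alginate's in vitro benefit may itself come from binding calcium, in which case subtracting meal 1 − meal 4 could remove part of the effect of interest.

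These points limit the remedy. They do not make meal 2 versus meal 3 a test of reduced inhibition. An analysis plan that is not at hand would not settle the matter, because the protocol itself fixes the outcome, the meals, the test and the sample size.

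**Conclusion.** The concern holds as a mismatch between hypothesis and test. A significant meal 2 − meal 3 difference would show that more, or less, iron is absorbed from beads than from the capsule when calcium is given. It would not show that alginate reduces calcium's inhibition. With no additive modification, n = 8 and SD 2.8, a general effect the size of the primary target gives a significant result in about 58% of trials, or about 19% under an assumed 50% proportional inhibition.

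The interaction can be estimated from group A without further visits, but the trial is not sized for it. The detectable value at n = 8 is about 4.6 points at correlation 0 and about 3.2 at correlation 0.5, assuming SD 2.8 for both differences, and it worsens with the expected losses. Severity: should-fix. It affects the interpretation of a secondary aim and leaves the primary analysis untouched.

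**What to change.** 1. Keep meal 2 versus meal 3 as the powered secondary comparison. In Sections 1.2.1, 4 and 14.2, limit its conclusion to *more iron is absorbed from beads than from the capsule when calcium is given*.
2. Add to Section 14.2 the per-volunteer group A contrast (meal 2 − meal 3) − (meal 1 − meal 4), computed on fractional absorption as in Section 14.3 so that each meal is adjusted for its own dose. Fix the scale (percentage points or ratio) in advance and report the contrast with a 95% CI. Any statement that alginate reduces calcium's inhibition should rest on this contrast.
3. Show meal 2 − meal 1 and meal 3 − meal 4 as descriptive only.
4. State the limits: the detectable values above over a range of correlations and completers; the +2b bias under a linear visit trend; dose matching only within pairs 1/4 and 2/3; and calcium already in the beads, so that the contrast concerns only the added 600 mg.

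The cost is text in Sections 1.2.1, 4, 14.1 and 14.2, with no new visits or samples. The price is candour: the calcium-binding question will be answered by an estimate that is probably wide, not by the 80%-power test now implied.
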